### 5.8.1. Primary caregiver FGDs

Eight FGDs will be conducted with primary caregivers approximately 9-12 months after the HFI roll-out; four FGDs will be held with primary caregivers over 30 years, and four with caregivers under 30 years. As outlined in Table 5.3, we have designed a matrix which distributes the FGDs across the desired categories.

**Table 5.3 Sampling matrices for primary caregiver FGDs**

|           | HFI health centers |         | Standard care health centers |         |
|-----------|--------------------|---------|------------------------------|---------|
|           | <30 yrs            | >30 yrs | <30 yrs                      | >30 yrs |
| HC # 1-5  | FGD 1              | FGD 2   | FGD 5                        | FGD 6   |
| HC # 6-10 | FGD 3              | FGD 4   | FGD 7                        | FGD 8   |

The ten health centers in each of the ACT PRIME study arms will be numbered and inserted into the matrix above. One village in close proximity to one of the health facilities on each of the lists (health centers 1-5, and 6-10) will be selected using convenience sampling to include in each of the primary caregiver FGDs. Different health centers and different villages will be selected for each FGD. Local leaders will be asked to help identify and invite 6-12 representatives from the specified target group to participate in the FGDs.

A moderator and an assistant will lead the discussions in the local language (Japadhola or Swahili) using the FGD guides (Appendix X). During the FGDs, participants will be encouraged to share all thoughts and opinions. All FGDs will be recorded using a digital voice recorder, provided informed consent is given by participants. Hand-written notes detailing respondent identification numbers and verbal and non-verbal participant responses will be made in all FGDs.

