#### **4.4.2. Rich description of context**

Rich descriptions of contextual factors will be collected in all IDIs and FGDs in order to identify any contextual factors participants feel may have affected the impact of the intervention.

Representatives from a randomly selected cross-section of health centers and communities will be invited to participate, and district officials will be purposively selected to represent those with most insight into the intervention process.

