## 5.3. STUDY POPULATION

Within the seven sub-counties of the study area, there are 22 lower-level government run health facilities, including 17 level II health centers, and 5 level III health centers; 20 will be included in ACT PRIME. These 20 health centers will be randomly allocated to the health facility intervention arm or the standard care arm for a total of 10 health facilities in each arm. Clusters to be included in ACT PRIME are defined as the catchment areas of the health centers including households that are located within a 2 km radius of the facilities. Only households located within the clusters will be included in the sampling frame for ACT PRIME. ACT PROCESS follows the same sampling frame as ACT PRIME; participants for each type of data collection methodology are defined below.

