### **5.3.5. Focus group discussions**

We will conduct up to 16 FGDs with primary caregivers and community health workers from the study area selected by convenience sampling.

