## **5.5. HEALTH WORKER COMMUNICATION ASSESSMENTS AND PATIENT EXIT INTERVIEWS**

We plan to conduct communication assessments with health workers from both the HFI and standard care arms. The purpose of the assessments is to evaluate and compare the communication between health workers and patients immediately before and after HFI training in ‘communicating with patients’ and then during the study period. Health worker/caregiver interactions during consultations will be audiotaped and assessed using a validated measurement methodology, the Measurement of Patient-Centered Communication (MPCC) (Appendix I). The MPCC scores assessments according to three elements of patient-centered communication: 1) exploring the disease and the illness experience, 2) understanding the whole person, and 3) finding common ground [44]. In addition to the recorded interactions, consenting caregivers will be interviewed immediately on exit from the consultation to give their view of the quality of the interaction with the health worker. The purpose of the interviews is to determine the level of satisfaction of caregiver with the health facility visit.

Health workers from both the HFI and standard care arms available on the day of the communication assessment will be selected using convenience sampling, and invited to participate. At least one health worker from each facility, will be included. At least three interactions, and up to five interactions, will be recorded with each health worker. Written informed consent to conduct the assessments will be obtained from health workers before beginning (Appendix J) as outlined in section 8.2. Demographic information on the health worker will then be obtained (Appendix K).

Once a health worker has been selected and provided informed consent, caregivers who will have a consultation with that health worker will be selected using convenience sampling from the available patients visiting the health center on the day of the health worker communication assessment.

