## **5.7. SEMI-STRUCTURED QUESTIONNAIRES**

We plan to administer semi-structured questionnaires with health workers from HFI and standard care arms, and private drug shop workers. The purpose of the questionnaires is to collect information on the contextual factors and perceptions of the HFI as it is being implemented as well as the expected and unexpected impacts of the HFI. Written informed consent to conduct the interviews and administer the questionnaires will be obtained from all participants before beginning (Appendix T) as outlined in section 8.2. The interviews with health workers and private drug shop workers will be conducted approximately 9-12 months after the HFI roll-out.

Health workers from HFI and standard care arms will be selected by convenience sampling to ensure at least one health worker from each health facility participates in an interview. We plan to complete up to 10 interviews with health workers in both ACT PRIME arms, 20 in total. The draft questionnaire (Appendix U) will be piloted prior to the onset of the study, and will be refined if necessary.

Private drug shops workers will be randomly selected from the database developed for the Tororo District Survey Project. We plan to complete up to 10 interviews with private drug shop workers. The draft questionnaire (Appendix V) will be piloted prior to the onset of the study, and will be refined if necessary.

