**Table 5.2 FGD target populations**

| Target group            | Definitions                                                                      | FGD characteristics                                                                                                                                                                       |
|-------------------------|----------------------------------------------------------------------------------|-------------------------------------------------------------------------------------------------------------------------------------------------------------------------------------------|
| Primary caregivers      | Person primarily responsible for daily care of young children (generally female) | Groups to be stratified by age (< 30 years vs. > 30 years), health center (communities from each health center in ACT PRIME will be represented)                                          |
| Community health worker | Person providing health care through the Village Health Team                     | Health center (communities from each health center in ACT PRIME study will be represented), distance to a health center (within or outside of a 2km radius of an ACT PRIME health center) |

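### Caregiver focus groups reach 8 of 20 centres, chosen by convenience, although the plan says every centre and, elsewhere, random selection; drug shops are drawn with no stated link to arm

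*Supplement*

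**What the plan says.** **Coverage.** Section 5.3 randomises 20 health centres, "for a total of 10 health facilities in each arm". The caregiver row of Table 5.2 states that "communities from each health center in ACT PRIME will be represented". Section 5.8.1 states: "Eight FGDs will be conducted with primary caregivers", four groups aged over 30 and four under 30. The ten centres of each arm are numbered and split into two lists of five. The rule below Table 5.3 is "One village in close proximity to one of the health facilities on each of the lists", chosen by convenience, and no centre or village is used for more than one group.

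**Selection.** Section 4.4.2 concerns the contextual material from all in-depth interviews and FGDs: "Representatives from a randomly selected cross-section of health centers and communities will be invited to participate". Section 5.3.5 says: "We will conduct up to 16 FGDs with primary caregivers and community health workers from the study area selected by convenience sampling". Sections 5.8.1 and 5.8.2 repeat convenience for the villages.

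**Drug shops.** Secondary objective 4 includes impacts on the private sector. Table 4.1 assigns drug shops to the context and impact components, with a maximum of 10. Section 5.7: "Private drug shops workers will be randomly selected from the database developed for the Tororo District Survey Project". The health worker questionnaires have a number for each arm (section 5.3.4); the shops do not.

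**Recordings and exit interviews.** Section 5.5 says that the caregivers of a selected health worker "will be selected using convenience sampling from the available patients visiting the health center" on the day of the assessment.

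**The concern.** The coverage statement and the sampling rule cannot both be met, and neither can the random and the convenience statements. A report written from Table 5.2 or section 4.4.2 would describe a wider and less selected caregiver sample than section 5.8.1 produces. Convenience choice tends to favour places that are easy to reach or well disposed, and local leaders then help to identify the participants.

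The drug-shop gap is of another kind. The form asks whether customer numbers, and malaria customers in particular, have changed over the last year. Such an answer bears on the health facility intervention (HFI) only if it is known whether the shop serves an HFI area, a standard-care area or neither.

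For the recordings, free choice among the patients present leaves room for selection, because no masking of the person choosing is described and the cycles are timed around the training.

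**Working it through.** **The plan's own total.** Table 5.3: 2 arms × 2 lists × 2 age strata = 8 caregiver groups. Table 5.4: 2 arms × 2 lists × 2 distance strata = 8 community health worker (CHW) groups. 8 + 8 = 16, the maximum in section 5.3.5.

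**Centres reached by caregiver groups.**
- Rule as tabulated (one centre per group, all different): 8 × 1 = 8 of 20, or 40%. That is 4 of 10 in each arm, and 12 centres have no group.
- Loosest reading (one village from each list in every group): 8 × 2 = 16 of 20, or 80%. This fits Table 5.3 poorly, since each group there sits in the row of a single list, and it still falls short of every centre.
- Within an arm, each list supplies one younger and one older group, and centres may not repeat. A sampled centre therefore contributes one age stratum only, so age and centre cannot be separated.

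**Centres reached by CHW groups.** Section 5.8.2 puts five villages from five different centres in each group: 2 arms × 2 lists × 5 = 20 of 20 centres, 8 × 5 = 40 villages, and each centre in both distance strata. The same rule applied to caregivers would reach all 20 centres with the same eight groups, each centre in both age strata. With 6 to 12 participants per group, that is 6/5 = 1.2 to 12/5 = 2.4 per village.

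**Random or convenience.** Section 4.4.2 says random for centres and communities. Sections 5.3.5, 5.8.1 and 5.8.2 say convenience for the FGDs, and section 5.6 says convenience for the HFI health worker interviews, which section 4.4.2 also covers.

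**Drug shops.** The documents give no distribution of shops, so the shares below are assumptions. With 10 independent draws and a share q of shops in HFI catchments (all others in standard-care catchments), P(X = x) = C(10, x) q^x (1 − q)^(10 − x).

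| Assumed q | P(exactly 5:5) | P(7:3 or more uneven) |
|---|---|---|
| 0.3 | 0.10 | 0.66 |
| 0.4 | 0.20 | 0.44 |
| 0.5 | 0.25 | 0.34 |

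Check at q = 0.5: 2 × 176/1024 = 0.344.

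If only a share t of listed shops lies in any study catchment, split evenly by arm, the expected number per arm is 10 × t/2:

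| Assumed t | Expected per arm | P(smaller arm has 2 or fewer) |
|---|---|---|
| 0.8 | 4 | 0.33 |
| 0.6 | 3 | 0.68 |
| 0.4 | 2 | 0.93 |

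A fixed 5 v 5 would not support a test either. Fisher's exact test gives p = 0.048 for 5/5 v 1/5 and p = 0.21 for 4/5 v 1/5.

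**The case against.** Much can be said for the design.

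- A reader might infer that the comparison of arms is lost. It is not: Table 5.3 gives four caregiver groups per arm with the same age strata, as section 5.8 intends.
- A reader might infer that 12 centres have no caregiver voice. They lack a focus group only. Section 5.3.2 aims for at least one health worker in every facility of both arms, three to five interactions each in three cycles, with exit interviews for all consenting caregivers.
- A reader might infer that every centre was promised at random. These are two separate statements: Table 5.2 promises every centre, and section 4.4.2 a random cross-section. No passage promises both.
- The weakness does not extend to all community samples. The CHW groups cover every centre; only their convenience selection conflicts with section 4.4.2.
- No passage promises a drug-shop comparison by arm. Shops were not randomised, section 7.1 names no comparison groups, and caregiver groups also discuss sources of treatment. Section 5.3 says that the study follows the ACT PRIME sampling frame, but section 5.7 does not say that the database draw is limited to it. The first page of the shop form is not shown, so it may record location or arm.
- That the people choosing caregivers know the arm is an inference. Section 5.1 assigns a field team separate from ACT PRIME, and eligibility is screened on a fixed form.

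All of these stand, and they limit the point. None removes the conflict on coverage, the conflict on selection, or the missing statement of how shops relate to arm. It is also fair that convenience sampling is openly declared and is ordinary in qualitative work; the fault is that other sections say something else.

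**Conclusion.** The point holds in this limited form. For caregiver FGDs the stated coverage of every centre is not delivered: 8 of 20 centres, or at most 16 on a strained reading. That count needs no assumption beyond the rule in section 5.8.1. The random selection in section 4.4.2 contradicts the convenience sampling in sections 5.3.5, 5.8.1 and 5.8.2.

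The drug-shop matter is a design gap and breaks no promise. Shops are the only private providers sampled, and nothing stated ties them to exposure. The probabilities of an uneven split only illustrate the risk. They rest on assumed shares and independent draws, and the range is wide, so no single figure should be cited as the plan's risk.

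The choice of caregivers for recording is an avoidable opening for selection, not a demonstrated bias. The whole point deserves correction but does not threaten the main comparison.

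**What to change.** 1. **Caregiver coverage.** Either adopt the rule of section 5.8.2 for caregivers (villages from five centres in each group, so the same eight groups reach all 20), or correct the caregiver row of Table 5.2 to 8 of 20 centres. Leave the CHW row as it is, since it is right.
2. **Selection.** Draw the villages, and the centres if only eight are used, at random from the numbered lists and the GPS list. Otherwise amend section 4.4.2 to say convenience, for the health worker interviews as well.
3. **Drug shops.** Draw at random within HFI and standard-care catchments, for example 5 and 5, record the arm, and state that the comparison is descriptive.
4. **Recordings.** Take consecutive eligible caregivers seen by the selected health worker, up to the planned three to five.

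The numbers of groups, shops and interviews stay the same. The cost is some rewording and a random draw. Some drawn villages will be harder to reach, and multi-village groups mean more travel for participants and only one or two voices per village.

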### 5.8.2. Community health worker FGDs

We plan to conduct eight FGDs with CHWs approximately 9-12 months after the HFI roll-out. As outlined in Table 5.4, we have designed a matrix which distributes the 8 FGDs across the desired categories.

**Table 5.4 Sampling matrices for CHW FGDs**

|              | HFI health centers |       | Standard care health centers |       |
|--------------|--------------------|-------|------------------------------|-------|
|              | < 2km              | ≥ 2km | < 2km                        | ≥ 2km |
| HC #
1-5  | FGD 1              | FGD 2 | FGD 5                        | FGD 6 |
| HC #
6-10 | FGD 3              | FGD 4 | FGD 7                        | FGD 8 |

The ten health centers in each of the ACT PRIME study arms will be numbered and inserted into the matrix above. One village located < 2km, and one ≥ 2km, from each of the health facilities, will be selected using convenience sampling from a list generated by previous GPS mapping. Local leaders will be asked to help identify and invite all CHWs from their village (typically two per village) to participate in the FGDs. A total of 5 villages will be represented in each FGD, representing the catchment areas of 5 different health centers.

A moderator and an assistant will lead the discussions in the local language (Japadhola or Swahili) using the FGD guides (Appendix Y). During the FGDs, participants will be encouraged to share all thoughts and opinions. All FGDs will be recorded using a digital voice recorder, provided informed consent is given by participants. Hand-written notes detailing respondent identification numbers and verbal and non-verbal participant responses will be made in all FGDs.

## 5.9. STRUCTURED CONTEXTUAL RECORD

A structured contextual record will be used to collect details about factors that may affect implementation and impact of the HFI. Sources of information for contextual details include published and grey literature; radio, local television and newspaper reports; notices from the Uganda MoH, National Malaria Control Programme, and other national departments; internet sites of organizations and NGOs active in the area including WHO, other UN organizations, Malaria Consortium, AMREF; and other relevant sources of information. These sources of information will

be reviewed on a three-monthly basis by the implementation team and details will be entered into the structured contextual record (Appendix Z).

In addition, detailed data will be collected prospectively on coverage levels of key malaria control interventions across Tororo district as detailed in Table 5.5. These data will be collected through the UMSP sentinel site at Nagongera Health Center IV in Tororo district. Data on IRS coverage will come from the Uganda MoH and implementing partners. Data on ITN coverage and ACT use will come from the cross sectional surveys and outpatient surveillance system operated by the UMSP.

**Table 5.5 Malaria control intervention variables of interest**

| Category | Metric                                                                      | Source of data          |
|----------|-----------------------------------------------------------------------------|-------------------------|
| IRS      | – Date, formulation, and proportion of households sprayed                   | MoH records             |
|          | – Proportion of households with at least one bednet                         |                         |
| ITNs     | – Proportion of households with at least one ITN                            |                         |
|          | – Average number of nets per household                                      |                         |
|          | – Average number of ITNs per household                                      | Cross-sectional surveys |
|          | – Proportion of children under five who slept under any net the prior night |                         |
|          | – Proportion of children under five who slept under an ITN the prior night  |                         |
| ACTs     | – Proportion of febrile episodes in children treated with an ACT            | Cross-sectional surveys |
|          | – Proportion of antimalarial doses prescribed that were ACTs                | Outpatient surveillance |
|          | – Number of ACT doses prescribed at health care facility per month          | Outpatient surveillance |

## 5.10. SUPPLY OF DRUGS AND RDTs

We plan to collect data on the supply of artemether-lumefantrine and RDTs provided by the ACT PRIME Study to each of the HFI health centers using drug stock cards, and requisition and issue vouchers from the health centers and health sub-districts. Study personnel will collect the information during a one-day visit to the health facilities. The in-charge of the facility will be approached and informed about the surveillance activities. An information sheet (Appendix AA) will be used to describe the purpose of the activities and verbal consent to collect information will be obtained from the in-charge. Information will be collected on (1) supply and use of artemether-lumefantrine supplied by National Medical Stores (NMS) and ACT PRIME; and (2) supply and use of RDTs for malaria supplied by ACT PRIME (Appendix BB).

## 6 DATA MANAGEMENT

---

### 6.1. DATA MANAGEMENT

#### 6.1.1. Quantitative data

Quantitative data from the self-filled questionnaires, patient exit interviews, semi-structured questionnaires, structured contextual record, and supply records will be collected by the study team. Data from the paper questionnaires and data collection forms will be entered into an Access database by a data entry clerk and will be double entered to verify accuracy. Back-up files of databases will be stored after each data entry session. For quality control, query programs will be written into the database to limit the entry of incorrect data and ensure entry of data into required fields.

#### 6.1.2. Qualitative data

##### 6.1.2.1. *Self-filled questionnaires*

Qualitative data from the self-filled questionnaires will be typed into Word documents for export to NVivo qualitative data management software. All typed records will be checked for accuracy against the original questionnaires. Back-up files of word documents will be stored after each data entry session.

##### 6.1.2.2. *Health worker communication assessment*

All health worker communication assessments will be audiotaped using a digital voice recorder. Assessments will be transcribed and translated into English if necessary. Summaries of the assessments will be coded using an appropriate software package. All coded records will be checked for accuracy against the original recordings and field logs. The consultation recordings will be backed-up after each coding session.

